**Figure 1 F1:**
[figure not shown]
Study protocol. PERMA: Positive emotion, engagement, meaning, positive relationship and accomplishment, IBCT: Integrative-behavioral couple therapy.

### Ethical considerations

The Ethics Committee of Shahid Sadoughi University of Medical Sciences approved this study with code IR.SSU.REC.1398.140.

### Statistical analysis

Frequency, percentage, mean, and standard deviation will be used to measure descriptive data. Shapiro-Wilk's normality test will be applied to determine the normal distribution of quantitative data. Chi-square test will be done for comparing qualitative data. Parametric analytic statistical tests like ANOVA will be applied for the measurement of the two primary outcomes (fertility problems and satisfaction with the intervention method) if the data have a normal distribution. P-values 
<
 0.05 will be considered significant.

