**Materials and Methods:**

The content of the interventions was developed and adjusted based on a literature review and the opinions of experts. In this three-arm parallel randomized clinical trial, 42 couples undergoing infertility treatment will be allocated randomly into three groups (n = 14 couples/each). Group 1 will receive the PERMA intervention, group 2 will receive the IBCT intervention, and group 3 as the control group will receive an infertility treatment training program intervention. The primary outcome will be the fertility problems, which will be measured by completing a fertility problem inventory at baseline, as well as in the 5
${}^{\text{th}}$
 and 9
${}^{\text{th}}$
 wk as a follow-up. Another primary outcome, satisfaction with the intervention, will also be assessed in the 5
${}^{\text{th}}$
 and 9
${}^{\text{th}}$
 wk. The secondry outcome will be a positive pregnancy test at wk 12. The interventions will be conducted through a combination of face-to-face and online via WhatsApp.

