### Objects

The primary object is determining and comparing the mean scores of fertility problems in women, men and couples at the baseline of the intervention, at the end of the 5
${}^{\text{th}}$
 wk of the intervention, and one month after ending the intervention (in the 9
${}^{\text{th}}$
 wk) in the three study groups. The other primary outcome will be the mean satisfaction scores of the interventional method in women, men and couples at the end of the 5
${}^{\text{th}}$
 wk of the intervention and one month after the intervention (in the 9
${}^{\text{th}}$
 wk) in the three study groups. The secondary outcomes will be the frequency and percentage of pregnancy at the time of follow-up (in the 12
${}^{\text{th}}$
 wk) in the three study groups (Figure 1).

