### Sampling and sample size

The estimated sample size is 84 husbands and wives (14 couples in each group) based on a previous study (23) and considering α = 0.05, β = 90%, power = 80% and σ = 2.5, and 15% attrition rate. The statistical formula used for sample size determination was n = 2 (z 1-
α
 / 2 + z 1 -
β
)^2^

σ

^2^ / (µ1-µ2)^2^.

In this three-arm parallel randomized clinical trial, two intervention groups (the PERMA model and IBCT) and a control group (infertility treatment training program) will be studied. 42 couples will be allocated into the three groups randomly (14 in each). Written and verbal informed consent will be obtained from husbands and wives separately.

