### Outcomes

The mean scores of the fertility problems will be determined (assessed by the FPI) in the women, men and couples at the baseline of the intervention, at the end of the 5
${}^{\text{th}}$
 wk of the intervention, and one month after the termination of the intervention (in the 9
${}^{\text{th}}$
 wk) in the three study groups. Also, the mean score of satisfaction with the counseling method will be determined (assessed by the satisfaction questionnaire) in women, men and couples at the end of the 5
${}^{\text{th}}$
 wk of the intervention, and in the 9
${}^{\text{th}}$
 wk in all three groups. Occurrence of pregnancy will considered as a secondary outcome, defined as a positive pregnancy test, which will be assessed in the follow-up in the 12
${}^{\text{th}}$
 wk.

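### FPI is measured at baseline, but the only analysis named for it is an ANOVA conditional on a normality test, with no baseline covariate; a baseline-adjusted model would be more precise at almost no cost

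*Protocol article*

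**What the plan says.** The abstract of the protocol article makes FPI a primary outcome with a baseline measurement: "The primary outcome will be the fertility problems, which will be measured by completing a fertility problem inventory at baseline", and again at weeks 5 and 9. The Objects section states the primary aim as "determining and comparing the mean scores of fertility problems in women, men and couples at the baseline of the intervention", and at the two later times, in the three study groups. Baseline is therefore listed as one of the times at which means are compared.

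The Statistical analysis section gives the method in two steps. First, "Shapiro-Wilk's normality test will be applied to determine the normal distribution of quantitative data". Then "Parametric analytic statistical tests like ANOVA will be applied for the measurement of the two primary outcomes", which applies "if the data have a normal distribution". No covariate is named, and the type of ANOVA is not stated.

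The same sentence covers satisfaction with the intervention. According to the Outcomes section, satisfaction is scored at weeks 5 and 9 only, so it has no baseline value.

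**The concern.** In a trial of 14 couples per arm, the baseline value of the outcome is usually among the most useful covariates available. Chance differences between arms at baseline are large at this size. In a comparison of follow-up means they carry into the estimated effect in proportion to the baseline to follow-up correlation. Adjusting for baseline removes that component and reduces the residual variance. The measurement is already paid for, but the named analysis gives it no such role.

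Two further features of the stated method are worth changing. A preliminary test on the trial's own data decides whether the parametric method is used, so the primary method is settled only after the data are seen. FPI is to be reported for women, men and couples at three times. If the check is made separately for each, there are 3 × 3 = 9 decisions, and parts of one outcome could be analysed by different methods. Also, a between-arm comparison of baseline means in a randomized trial says nothing about the effect of the interventions.

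**Working it through.** **Inputs from the document.** There are 14 couples in each of three arms, 42 in total (Sampling and sample size). Attrition is 15%. FPI is measured at baseline, week 5 and week 9. The correlation r between baseline and follow-up FPI is not given, so it is an assumption here, shown at 0.3, 0.5 and 0.7.

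**The plan's own figure.** The sample size is justified by "considering α = 0.05, β = 90%, power = 80% and σ = 2.5, and 15% attrition rate" and the two-sample formula for means. The difference µ1 − µ2 is not stated, so 14 per arm cannot be reproduced directly. Working backwards, 12 evaluable couples × 1.15 = 13.8, which rounds to 14. At 80% power, 12 per arm implies a difference of 2.5 × √(2/12) × (1.960 + 0.842) = 2.86, or 1.14 SD. The formula has no term for r. I use 12 evaluable couples per arm (36 in total) below.

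**Chance baseline difference.** The standard error between two arms of 14 is √(2/14) = 0.378 SD. A gap of one standard error shifts an unadjusted follow-up difference by r × 0.378: 0.11, 0.19 and 0.26 SD at r = 0.3, 0.5 and 0.7.

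**Reading A: ANOVA on follow-up means without adjustment.** ANCOVA multiplies the residual variance by 1 − r², so the effective sample rises by 1/(1 − r²). Estimating the slope costs a factor of 1 + 1/(N − 5). With N = 36 this is 1 + 1/31 = 1.032.

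| r | 1/(1 − r²) | after slope cost |
|---|---|---|
| 0.3 | 1/0.91 = 1.10 | 1.07 |
| 0.5 | 1/0.75 = 1.33 | 1.29 |
| 0.7 | 1/0.51 = 1.96 | 1.90 |

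At the back-calculated difference of 2.86, power with 12 per arm (normal approximation, slope cost ignored) moves from 80% to 83.6%, 89.9% and 97.5%.

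**Reading B: repeated-measures ANOVA over the three times.** Assume equal variances and equal correlations r between all pairs of times. In units of SD², per couple:

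- Variance of the mean of weeks 5 and 9, minus baseline: (1 + r)/2 + 1 − 2r = 1.5(1 − r).
- Variance of the mean of weeks 5 and 9 after ANCOVA on baseline: (1 + r)/2 − r² = (1 − r)(1 + 2r)/2.
- Ratio: 3/(1 + 2r).

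| r | change contrast | ANCOVA | ratio |
|---|---|---|---|
| 0.3 | 1.05 | 0.56 | 1.88 |
| 0.5 | 0.75 | 0.50 | 1.50 |
| 0.7 | 0.45 | 0.36 | 1.25 |

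ANCOVA is the more precise on both readings at every r shown. Reading A favours it most when r is high, and Reading B when r is low.

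**The case against.** The strongest reply is that the article does not say what type of ANOVA it means. It offers ANOVA as an example of a parametric test and lists baseline among the times compared, which is compatible with a repeated-measures analysis that uses all three measurements. A reader might infer that the plan compares unadjusted means and throws baseline away. The text does not establish that, and this part of the reply stands. It does not remove the point, because Reading B also loses to ANCOVA.

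A second reply is that a condensed article may leave covariates and model structure to a fuller document. That also stands, so the absence of detail is not the complaint here. The complaint concerns the method that is stated: a test family chosen by a normality check, for an outcome whose baseline is already collected.

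A third reply concerns size. A reader might claim a gain of a third or more as a fact. That needs r of at least 0.50, and after the slope cost even r = 0.5 gives 1.29. The document gives no r, and the exclusion of couples with severe FPI scores may lower it by restricting the range.

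Finally, a reader might argue that Shapiro-Wilk misses real skew at this size and so damages the analysis. For one assumed skewed distribution, Beta(5, 1.5), simulated detection was about 22% at n = 14 but about 73% with all 42 couples pooled, and the article does not say which would be tested. With 12 per arm from that distribution, the simulated type I error of one-way ANOVA was 4.7%. Nothing in the document links FPI to that shape. The objection to the normality check is therefore that it lets the data choose the primary method; inflated error has not been shown. Nor does the article say whether raw scores or residuals would be tested.

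**Conclusion.** The point holds as an improvement to the stated FPI analysis; it does not show that the plan is invalid. The gain in effective sample over unadjusted follow-up means is about 10%, 33% and 96% at r = 0.3, 0.5 and 0.7, less about 3% for the slope. Over a repeated-measures change contrast, the factors are 1.88, 1.50 and 1.25. These figures rest on an assumed r and, for the second set, on equal variances and correlations across the three times. The slope cost and the power figures also assume 12 evaluable couples per arm.

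Two limits apply. A reader might extend the adjustment point to both primary outcomes because one sentence covers both, but satisfaction has no baseline to adjust for. A between-arm test at baseline is the natural reading of the Objects section, but it is not stated outright.

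**What to change.** In the Statistical analysis section, name the FPI analysis as one of these:

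- ANCOVA of FPI at each follow-up on arm, with baseline FPI as covariate; or
- a linear mixed model of the week-5 and week-9 scores on arm, time, arm × time and baseline FPI. It should account for repeated measures and, where both spouses are analysed together, for clustering within couple.

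Remove the condition that lets a preliminary normality test choose the primary method. Check the model residuals instead, and give a permutation or bootstrap p-value as a sensitivity analysis. In the Objects section, report baseline FPI by arm descriptively and do not test it between arms.

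Satisfaction needs no baseline term.

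The cost is a change of analysis wording and one or two degrees of freedom. No new data are needed.

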## 3. Discussion

Nowadays, many couples face the challenge of infertility and the problems resulting from its treatment. Infertility causes stress and anxiety in infertile couples which affect their lives. Psychological problems also exacerbate infertility. Women undergoing infertility treatment with in vitro fertilization or other methods may experience a change in their quality of life, marital relationship, and sexual functions. Psychological interventions have a significant impact on reducing these problems of infertile couples (30, 31). The PERMA model is used to increase well-being and health (13), increase happiness, improve depressive symptoms (12), and increase personality strengths (32). The effect of behavioral therapy on infertile couples is significant, which enriches communication, increases marital satisfaction, protects relationships, and helps to solve problems (17). In the first phase of the present study, the content of the interventions' sessions was developed and adjusted based on a literature review and the opinions of expert panel members from various related disciplines. The intervention sessions will be conducted by trained and experienced counselors in all three groups. These packages can be used for raising optimism, increasing communication skills, and providing infertility treatment information to couples and other researchers.

There are five building blocks in the PERMA model that enable flourishing and improved mood. We have chosen this model to assess whether improving the mood, after practicing the domains of the PERMA model, can lead to amelioration of tolerance in couples and the mean scores of the FPI.

In the IBCT model, couples learn communication skills, problem-solving skills, behavioral exchange techniques, and empathetic joining. The communication training program leads couples to communicate better and improve their conflict-resolution skills. We expect improvement in communication skills to lead to improvement of the mean scores of the FPI.

Many patients with infertility who have psychological stress do not receive mental health services. Couples seeking infertility therapy should be informed about the treatment process because a lack of information leads to stress. Perhaps using an infertility treatment training program can reduce their stress.

Although men, similarly to women, need psychological interventions, they are not usually supported by support services. Therefore, the present psycho-social services will be provided to infertile couples; not only women will be considered but also their spouses. Therefore, in the present study via using the content of the intervention packages and comparing the results in the three groups (women, men, and the couples), we hope that perceived infertility-related stress decreases. We also will compare the mean satisfaction scores of the three intervention methods in the women, men, and the couples. Besides enhancing the marital status by employing such methods, couples' satisfaction with these interventions may lead them to recommend these methods to other couples, or they may be interested in continuing these intervention methods in the future or applying these methods for other problems in their marital life. In addition, a combination of face-to-face and online methods may be useful in infertility treatment at the time of outbreaks of COVID-19 or other similar diseases that necessitate social distance regulations.

It is hypothesized that PERMA, IBCT, and infertility treatment training programs will help reduce stress reaction mechanisms in the present study. Reducing psychological problems can have positive effects on infertile couples, and according to previous studies, PERMA and IBCT methods can have positive effects on reducing stress in infertile couples. This study provides a package of a series of exercises for couples who can continue to use them after their couple's sessions. Participation of couples is one of the strengths of the present study. Another strength is that sessions are not held in groups - there is just one couple in each session. Thanks to the positive content of couple's therapy approaches and routine care, the needs, and problems of these couples can be reduced by using these models. Other strengths of this study include the involvement of a specialist team such as a reproductive health specialist and psychologist, a fellow in infertility and a couple's therapy consultant, as well as a midwifery consultant. Another strength is use of the FPI, which considers many aspects of fertility problems such as social concerns, sexual concerns, relationship concerns, rejection of a childfree lifestyle, and the need for parenthood.

We hypothesize that through this study we will help infertile couples to first acknowledge their infertility and then be able to reduce their fertility problems by better tolerating, coping with and dealing with these problems, and also gaining skills in solving problems, and seeing other positive aspects of their lives. The results of the present study might be used by the Health Ministry to develop policies towards considering the mental health of couples during infertility treatment. In addition, by increasing successful pregnancy rates through reducing stress, these interventions could lead to a decrease in the number of fertility treatments needed and so also reduced costs and other burdens.

Limitations of the present study include that, due to the nature of the interventions, it is impossible to blind the couples or counselors to the intervention allocations.

## 4. Conclusion

This study will assess social, sexual, relationship and parenthood concerns. A combination of online and face-to-face interventions is appropriate for times of COVID-19 outbreaks. Couple's counseling may provide better outcomes for fertility problems in comparison with group counseling. A package for intervention sessions will be provided and the effectiveness of two psychological interventions (PERMA and IBCT) will be compared with the control group. This study will try to optimize resilience during infertility treatment through learning better relationship and problem-solving skills, which may also have an indirect impact on pregnancy rate, burden of infertility, and costs of treatment due to increased effectiveness.
